## Abstract

**Introduction:**

Balance disturbances in Parkinson’s Disease (PD) are usually assessed in a single-task as well as standard balance physiotherapy is carried out in isolated environments. Conversely, daily activities are developed in highly challenging environments. Although functional balance training (FBT) is included in the latest protocols, several methodological issues have not yet been considered. In the proposed single-blinded randomized control trial with crossover (NCT04963894), the aims are (1) to quantify the effects achieved by domiciliary FBT (balanceHOME program) in participants with and without cognitive impairment, and (2) to compare them with the effects of a passive-control period and a conventional face-to-face physiotherapy program for PD.

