Balance alterations in PD are usually assessed in a single task. The most common tests are based on static and dynamic balance, where the patient controls the CoP in a static position (e.g., standing) (Negrini et al., 2017; Giardini et al., 2018; Soke et al., 2019) or during motion in direction to the different LoS (Kara et al., 2012; Carpinella et al., 2017; Soke et al., 2019). To this assessment methodology, it is common to add the blockade of the different systems that participate in balance regulation, either by closing the eyes or placing foam under the feet. Similarly, standard balance physiotherapy is carried out in isolated environments with exercises focused on single tasks or similar scenarios to those of the evaluation (Giardini et al., 2018). Conversely, daily activities are developed in highly challenging environments, which have been addressed in previous publications with Wii balance games (Yen et al., 2011; Zalecki et al., 2013; Carpinella et al., 2017; Negrini et al., 2017; Feng et al., 2019; Yuan et al., 2020), dual-task exercises within daily activities (Conradsson et al., 2015; Wong-Yu and Mak, 2015a, 2015b; Atterbury and Welman, 2017; Perumal et al., 2017; Santos et al., 2017; Wallén et al., 2018; Leavy et al., 2020), and single daily activities training (Smania et al., 2010; Kara et al., 2012b) including postural transferences (Millage et al., 2017; Soke et al., 2019). Although functional balance training (FBT) is included in the latest protocols, which consists of daily activities with feasible settings for older adults with PD, there are several methodological issues that have not yet been considered. One of these is the assessment methodology of the previous studies and the objectivity of the measurements, using in most cases, scales, and clinical tests only (Conradsson et al., 2015; Wong-Yu and Mak, 2015a,b; Atterbury and Welman, 2017; Perumal et al., 2017; Santos et al., 2017; Wallén et al., 2018; Leavy et al., 2020) instead of integrating biomechanical parameters of balance in different measurement conditions with a follow-up period after finishing the studied intervention (Kara et al., 2012b; Conradsson et al., 2015; Atterbury and Welman, 2017; Perumal et al., 2017; Santos et al., 2017; Soke et al., 2019; Leavy et al., 2020). Furthermore, the authors who inform significant improvement in balance biomechanics (Kara et al., 2012; Santos et al., 2017; Soke et al., 2019) do so in patients with normal cognition status and use habitual locations like a physiotherapy gym or hospital facilities. To respond to the challenges that emerged since the COVID-19 pandemic, such as the demand for rehabilitation programs that can be followed from home, the effect of domiciliary FBT and the long-term impact with adequate follow-up need still be determined, as well as the effects in people with PD in advanced stages where cognition is altered. For the foregoing, the aims of this study are (1) to quantify the effects achieved by domiciliary FBT on the biomechanics of balance, gait, perception of quality of life, cognitive and mental performance, and severity of PD in participants with and without cognitive impairment and (2) to compare them with the effects of a passive-control period and a conventional face-to-face physiotherapy program for PD. We hypothesized that balance home training based on functional exercises has a greater effect than the traditional physiotherapy group. If this hypothesis is confirmed, it will open the possibility of new rehabilitation strategies according to changes in post-pandemic therapeutic approaches, reducing morbidity, and saving costs to the healthcare system.

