### Assignment of interventions and blinding

2.3.

An external investigator will perform the randomization process (1:1). Stratified randomization will be carried out according to PD severity and general cognitive state and assigned to one of the two groups for crossover, EG or PCG. A matched-pairs design will be created in which participants were allocated to these two groups taking into consideration the outcomes, i.e., Hoehn and Yahr state (I-II-III-IV) and Mini Mental Parkinson Test score (≥ 25, normal cognitive function or ≤ 24, altered cognitive function) at T0. The principal investigators will be responsible for the management of participants’ appointments after being assigned by telephone. On the other hand, the physiotherapist evaluator will be blinded to the assignment of the groups. For this reason, it will be explained to the participants that they do not reveal information about their intervention during the assessment sessions. Due to the nature of interventions, the patients and the physiotherapist who develop the rehabilitation cannot be blind to the treatment to be performed, but the hypothesis of the study will be hidden. Additionally, after the consent signature, participants will be assigned a numeric code to hide the group of intervention.

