### Data collection, management, and statistical analysis

2.4.

Both evaluators (physiotherapist and neuropsychologist) will be responsible for exporting and filling in a database with variables from the scales and tests mentioned in Table 2 according to the code assigned to each patient to ensure his or her anonymity. To protect confidentiality during the study, the personal information of participants will be located separately from the main dataset on a local computer. The raw dataset will be maintained for 10 years after the completion of the trial with indefinite restricted access due to sensitive data. After the publication of the results trial, a fully anonymized patient-level dataset will be made publicly available on the registration trial website (clinicaltrials.gov). For participation in this study, no participant will receive any kind of incentives or compensation.

All analyses will be evaluated by intention-to-treat principles in terms of assignment to treatment and used a level of significance of 0.05. There are no interim analyses planned for this study. We will use the statistical software SPSS Statistics version 24.0 (IBM Corporation) for all the statistical analyses. Categorical variables were presented using frequency and percentage, and continuous variables as mean with standard deviation if they follow a normal distribution. To test for possible carryover effects of the experimental group, the sum of the values measured in the two periods for each subject will be calculated and compared across the two randomized groups (EG and PCG) using a test for independent samples (Serrao et al., 2019). There should be no difference if there is no sequence (balanceHOME program—usual daily activity or usual daily activity—balanceHOME program) effect.

To answer to the main aim of the study, a two-factor mixed multivariate analysis of variance (MANOVA) test was conducted to analyze the effects of within-subject factors (assessment times) and the between-subject factor (group) on the outcomes registered. The Bonferroni adjustment was used for *post-hoc* comparisons, and differences were declared statistically significant if the value of *p* was less than 0.05. Differences between groups for demographic outcomes were verified with a univariate analysis of variance (ANOVA) between-subjects test. Furthermore, to test for sex differences between groups, a chi-square analysis was used (San Martín Valenzuela et al., 2020b).

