
Another relevant aspect is that this protocol aims to solve is the inclusion of dual tasks in the evaluation of balance. Biomechanical balance is usually evaluated as single-tasks on the dynamometric platform (Smania et al., 2010; Kara et al., 2012; Santos et al., 2017; Soke et al., 2019). Complementing the static balance test with dual tasks would provide results of balance performance in real-world situations. Previously, the impact of dual tasks on the gait of trained and untrained people with PD has been determined, finding that verbal secondary tasks have a greater impact on motor performance than visual or motor secondary tasks with the arms (San Martín Valenzuela et al., 2020a,b). In this way, the balanceHOME protocol pretends to resolve methodological issues and research questions relevant to the advancement of physical rehabilitation of balance in the population with Parkinson’s disease.

This protocol will make it possible to facilitate highly challenging functional balance exercises for people with PD at their homes, using common materials of daily use. Similarly, the objective assessment methodology and the balanceHOME protocol will allow us to identify small changes in the balance performance of people with different stages of disease severity and to determine the effectiveness of the home program in people without and with cognitive impairment, which has not been done until now as we will be able to establish the scope that physiotherapy has when it is applied in patients with motor and cognitive failures. Unlike the authors who report improvements below 50% in objective parameters, we think that the structured and progressive dynamics of balanceHOME program can exceed these values of improvement in both dynamic and static balance in single and dual conditions, while performing secondary cognitive and motor tasks of the arms during standing balance maintenance. Furthermore, due to the convenience of home rehabilitation, we think that the effects may achieve better retention during the follow-up period than standard control therapy. This protocol aims to promote change in functional balance physiotherapy both in evaluation and rehabilitation, bringing day-to-day conditions closer to clinical practice.

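### Aim 1 asks for the home programme's effect with and without cognitive impairment, but the analysis fixed for the main aim has only time and group as factors and cannot give it

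*Protocol article*

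**What the plan says.** - **Aim.** The Abstract sets out to quantify effects "in participants with and without cognitive impairment". The Introduction lists the outcome domains, ending with "severity of PD in participants with and without cognitive impairment". The Discussion promises "to determine the effectiveness of the home program in people without and with cognitive impairment" and presents this as something not done before.
- **Allocation (section 2.3).** "Stratified randomization will be carried out according to PD severity and general cognitive state". The cognitive split is an MMP score of 25 or more against 24 or less, and severity is H&Y stage I to IV. This covers the experimental group (EG) and the passive control group (PCG). The active control group (ACG) is not randomised.
- **Analysis (section 2.4).** For the main aim, "a two-factor mixed multivariate analysis of variance (MANOVA) test was conducted". The within-subject factor is assessment time and the between-subject factor is group.
- **Sample size (section 2.2.4).** 93 people, for f = 0.15, 5% two-tailed significance, 95% power and the groups EG, PCG and ACG. No cognition term is mentioned.

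No cognition term, cognition interaction, cognitive subgroup analysis or H&Y term appears in the analysis text.

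**The concern.** A time-by-group model estimates how change differs between groups, averaged over whatever mix of cognitive states was recruited. It yields no effect for impaired participants, none for unimpaired participants, and no comparison of the two. Yet the cognitive split is part of the first aim, is defined by a cut-off, is used in the allocation, and is offered as the trial's novelty.

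If the plan is followed, the question stays open. If it is not followed, any result by cognition will be an analysis chosen after the fact. A reader could then take a non-significant result in a small impaired stratum as evidence of no benefit, although the trial was never sized to show that.

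**Working it through.** **1. Aim against model.** The aim needs an effect in each MMP stratum. The model has group, time and group × time. No contrast of those terms isolates a stratum, so the mismatch follows from the text without arithmetic.

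**2. Reproducing the plan's 93.** Repeated-measures ANOVA, group × time, noncentral F with λ = f²·N·m/(1−ρ), df1 = (k−1)(m−1), df2 = (N−k)(m−1). From the document: f = 0.15, k = 3, alpha 0.05, power 95%. Not stated, hence assumed: the number of measurements m and their correlation ρ.
- m = 6, ρ = 0.5: λ = 0.0225 × 93 × 6/0.5 = 25.1, df 10 and 450, power 0.952. N = 93 is reproduced.
- m = 3: N = 93 needs ρ of about 0.67. At ρ = 0.5, power at 93 would be 0.81.

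Both variants that reproduce 93 are carried forward. Neither contains cognition.

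**3. Power for the cognition question at N = 93.** Let p be the impaired share. The document gives no expected share for this sample, so 20–50% is assumed. Suppose f = 0.15 holds in the unimpaired and no effect in the impaired. Then f_int = 0.15·√(p(1−p)), λ = f_int²·93·m/(1−ρ), df1 = 2(m−1), df2 = (93−6)(m−1). For p = 0.4, m = 6, ρ = 0.5: f_int = 0.0735, λ = 0.0054 × 93 × 12 = 6.03, power 0.32.

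In the last three columns the first figure is for m = 6, ρ = 0.5 and the second for m = 3, ρ ≈ 0.67.

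| p | Impaired n | f_int | Power, three-way term | Power for f = 0.15 in impaired alone | N for 95% power, three-way |
|---|---|---|---|---|---|
| 20% | 19 | 0.060 | 0.21 / 0.24 | 0.25 / 0.27 | 567 / 572 |
| 30% | 28 | 0.069 | 0.28 / 0.31 | 0.38 / 0.41 | 432 / 437 |
| 40% | 37 | 0.073 | 0.32 / 0.35 | 0.52 / 0.54 | 379 / 382 |
| 50% | 46 | 0.075 | 0.33 / 0.37 | 0.64 / 0.66 | 364 / 367 |

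**4. Precision of the randomised comparison.** Take 31 each in EG and PCG (93/3), first period, in SD units of the change score. The SE of the overall difference is √(2/31) = 0.254. The SE of the difference between strata is √(2/(31p) + 2/(31(1−p))), which is 0.254/√(p(1−p)). That gives 0.635, 0.554, 0.518 and 0.508 for p = 20%, 30%, 40% and 50%, or 2.5 to 2.0 times the overall SE. The 95% half-width in the impaired stratum is 1.96 × 0.254/√p: about 1.11 SD at 20% and 0.70 SD at 50%.

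**5. What the stratification factors add to the group × time test.** If stratum S shifts a person's level by b at every visit, b·S cancels from that person's change between visits. With complete data, adding S as a time-constant covariate leaves the group × time estimate and its error unchanged. MMP and H&Y help that test only through their interactions with time, that is, as far as they predict change.

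**The case against.** **The article is condensed.** A fuller protocol or SAP may hold the subgroup model, and covariate lists are often left there. This would excuse silence. It does not excuse section 2.4, which names the model, counts its factors and says that it answers the main aim. For the H&Y term taken alone the objection has more force.

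**The aim is not uniform.** The Introduction's hypothesis and the first restatement of the aim in the Discussion do not mention cognition. That is true, but the Abstract, the Introduction's aims and the close of the Discussion all do.

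Stronger readings that the documents do not support:
- *The stratification is wasted.* It still balances EG and PCG on MMP and H&Y, and it helps a stratum-specific analysis.
- *The randomised comparison is biased, or adjustment would cut its error variance by a known amount at no cost.* Leaving out balancing variables can make a test conservative, but it does not bias the EG/PCG contrast. Step 5 shows that a gain in the group × time test depends on how well MMP and H&Y predict change, for which the document gives no figure. Adjustment also costs degrees of freedom.
- *About 40% of this sample will be impaired.* The Discussion's 40% is a background figure for mild cognitive impairment at an earlier disease stage. It is not the expected share with MMP ≤24 among H&Y I–IV participants.
- *Every comparison ignores matching.* Time comparisons are within-person. Section 2.3 does mention matched pairs, but it does not say how pairs are formed, so a loss from ignoring them cannot be sized.

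**Conclusion.** The point holds as a mismatch between a stated aim and the analysis stated to answer it. Followed as written, the plan delivers one effect averaged over cognitive status and leaves the with-and-without-impairment part of Aim 1 unanswered.

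Adding the missing term makes the question answerable by estimation, not by a confirmatory test. Power for the three-way term at N = 93 is 0.21–0.37. That range rests on an assumed 20–50% impaired, an effect of f = 0.15 confined to the unimpaired, and the two assumed settings that reproduce 93. A smaller difference between strata would have less power.

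Omitting MMP and H&Y matters differently by comparison. Between EG and PCG it may cost some precision, by an unknown amount. Against the non-randomised ACG, imbalance in either factor can confound the result.

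**What to change.** - In section 2.4, add MMP stratum (≤24 or ≥25 at T0) to the model, with its group × time interaction.
- Report the group effect on change with a 95% CI in each MMP stratum, and the CI of the interaction.
- State that this is estimation only, because the 93 was sized for three groups with no cognition term.
- Include MMP and H&Y with their interactions with time. For EG against PCG this helps as far as they predict change. For comparisons with the ACG it reduces confounding by these two factors.
- Reword the Discussion's promise to determine effectiveness in both cognitive groups as estimating the effect in each, with its uncertainty.

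No new data, visits or participants are needed, since both measures are already taken at T0. The cost is a few degrees of freedom and wide stratum intervals. With three visits, the MMP three-way term takes (3−1)(2−1)(3−1) = 4. H&Y as four categories takes 3, and a further 3 × 2 = 6 for its interaction with time.

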### Study design

2.1.

The balanceHOME trial is designed as a randomized, controlled, and blind evaluator trial with a crossover intervention group. To write this protocol was used as a guide the Standard Protocol Items for Randomized Trials (SPIRIT) guidelines (Chan et al., 2013) and the Consolidated Standards of Reporting Trials statement for randomized controlled trials (Moher et al., 2010). The SPIRIT guidelines can be consulted in Supplementary material 1. Once the study was designed, it was registered on ClinicalTrials.gov (NCT04963894) on 15 July 2021 with the approval information of the Human Research Ethics Committee of the Experimental Research Ethics Commission of the University of Valencia obtained (Supplementary material 2).

The balanceHOME will be started with a baseline assessment session (T0) and followed by random allocation to one of two study groups: the experimental group (EG) or the passive control group (PCG). Additionally, a third group of participants with PD who habitually developed a conventional group physiotherapy program (Active Control Group, ACG) will be included in the evaluation process. At the end of the interventions (8 weeks), a post-training evaluation (T1) will be carried out, and subsequently, a follow-up assessment (T2) 8 weeks after the physiotherapy programs have finished. At this point, patients from PCG will switch with EG to receive the functional balance home program. The EG will follow a 4-month washout period (Serrao et al., 2019) before continuing as passive control participants (see Figure 1). The crossover design allows to control the intra-individual changes (due to personal characteristics and disease presentation), offer all the research benefits to the participants, and maximize the sample size it can achieve.

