#### Outcomes and participant timeline

2.2.3.

First, during the enrolment assessment, a standardized neurological clinical interview for Parkinson’s Disease (Supplementary material 4) will be performed. This interview includes questions related to habits, disease start, education, and working life. At the same time, weight, height, and body mass index will be measured with a wall stadiometer and a TANITA SC-240MA scale. The length of the lower limbs will also be measured during standing position with a tape measure from the anterior superior iliac spine and the medial malleolus. Asymmetries between the lower extremities greater than 1 cm will be considered within the first exclusion criteria (comorbidities that affect balance or gait). As mentioned above, each phase of the study has three evaluation moments: baseline (T0), post-8-week-training (T1), and follow-up (T2) at 8 weeks after the physiotherapy programs have finished. Assessments will be performed by a different physiotherapist from recruitment and treatment besides a neuropsychologist, both blinded to the treatment assignment. The participants will be evaluated in an ON-medication state (1 h after the dopaminergic dose) on the schedule described in Figure 1. In each measurement session, the severity of the disease (Hoehn and Yahr, 1967; Fahn et al., 1987), cognitive and mental status (Hamilton, 1959, 1960; Mahieux et al., 1995; Dubois et al., 2000; Marinus et al., 2003), perception on quality of life (Peto et al., 1995; Powell and Myers, 1995; Sandín et al., 2020), and balance and gait performance will be registered through clinical tests (Tinetti, 1986; Giladi et al., 2000; Kegelmeyer et al., 2007; Franchignoni et al., 2010) as well biomechanics instruments. Table 2 shows the scales and clinical tests that will be used to evaluate the participants. For balance biomechanics, assessment will be used a dynamometric platform (Dinascan/IBV Biomechanics Institute of Valencia, Valencia, Spain) and the NedSVE®/IBV software (version 5.3.0.1, Biomechanics Institute of Valencia, Valencia, Spain). Balance will be assessed through the Romberg tests under four static conditions with increasing difficulty (see Figures 2A,B): (i) eyes open; (ii) eyes closed; (iii) eyes open on a foam rubber; and (iv) eyes closed eyes on the foam rubber (thickness of 9 cm, 56.7 kg/m3 of density, and resistance of 25%) (Escamilla-Martínez et al., 2021). Participants were asked to find the most stable position while barefoot with their arms relaxed on either side of the body, with their heels together and toes apart at a 30° angle. Additionally, four static functional balance tests will be assessed, using the Romberg test protocol with their eyes open: (i) to see the time on an analogy clock (visual); (ii) to answer a simple question (verbal); (iii) to pour the contents of one glass into another (lower motor); and (iv) to simulate comb the hair (upper motor). The instructions for each task were standardized to ensure uniform execution of the gesture. Participants will be asked to remain as still as possible with their heads in a neutral position and their gaze forward, except for the lower motor test where they will be allowed to observe their hands. Each test will last for 30 s and will be recorded two times. Finally, dynamic balance will be assessed with stability limits and rhythmic weight shift tests on the platform (Balaguer García et al., 2012). In the stability limits test, participants from the Romberg position will have to move a cursor (which reflected the position of their CoP) toward eight targets (front, front-right, right, rear-right, rear, rear-left, left, and front left) visualized on a computer monitor placed in front at their eye level. Once the target is reached, the subject will have to maintain the posture with the CoP displaced at the limit of stability until the end of the 8 s of each test (Balaguer García et al., 2012). On the other hand, in the rhythmic weight shifts tests, subjects will have to move their CoP to the direction and velocity of a moving target visualized on the computer monitor (Balaguer García et al., 2012). Each dynamic test will be registered two times. As a result, the primary outcome of the study will be the CoP sway area, which is defined as the surface over which the CoP moves during the measurement and is a valid indicator of detecting postural control changes in dual-task conditions (Campolettano et al., 2020; Morenilla et al., 2020). The secondary outcomes are shown in Table 2 and consist of biomechanics and clinical variables related to static and dynamic balance.

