#### Sample size and recruitment

2.2.4.

The software G*Power v.3.1 (Faul et al., 2007) has been used to determine the necessary sample size to detect a change in the primary outcome CoP sway area and differences between the groups (EG, PCG, ACG), with a small-medium effect (*f* = 0.15), a statistical significance of 5% at the two-tailed level, and a power of 95%. As a result of the above, 93 people diagnosed with PD will be recruited. If 20% of possible dropouts are also considered during the study, the initial recruitment should be 112 people. The sampling process will consist in the consecutive non-probabilistic method, in which the selection of individuals is carried out based on the fulfillment of participation criteria. The recruitment of participants began on 1 July 2021 and we estimate its completion on 31 July 2023. The participant recruitment procedure consists of three steps. First, the neurorehabilitation center has selected the possible candidates for the study based on personal and clinical characteristics, asks them by email the authorization to send information about the study, and contacted them using their telephone number. Then, the principal investigators called potential candidates to resolve possible doubts and confirm their participation. Finally, a physiotherapist will assess the selection criteria for all the volunteers and will provide informed consent for their signatures. The recruitment process will be repeated to complete the number of participants estimated for the study, extending participation to a new clinical center or public hospital if necessary.

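### The model named for the main aim treats group as between-subject and states no treatment, period or sequence contrast, so it does not match the crossover in the design section

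*Protocol article*

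**What the plan says.** Section 2.4 of the protocol article answers the main aim with a two-factor mixed MANOVA "to analyze the effects of within-subject factors (assessment times) and the between-subject factor (group) on the outcomes registered". Assessment time is the only within-subject factor. Section 2.2.4 lists the groups as EG, PCG and ACG.

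Section 2.1 describes a crossover. After T2 of the first phase, "patients from PCG will switch with EG to receive the functional balance home program". For the other sequence, "The EG will follow a 4-month washout period", after which these people serve as passive controls. Section 2.2.3 adds that "each phase of the study has three evaluation moments" (T0, T1, T2). The abstract places two-thirds of participants in the crossover, while the remaining third attends the group programme only. Section 2.3 randomises 1:1 between EG and PCG; the ACG is not randomised.

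Section 2.1 gives statistical reasons for the crossover: "The crossover design allows to control the intra-individual changes", and it will "maximize the sample size it can achieve". The only analysis that section 2.4 says uses both periods is the carryover test, which compares each person's sum over the two periods between EG and PCG. That test does not estimate a treatment effect.

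**The concern.** Each randomised person supplies T0, T1 and T2 under balanceHOME and again under passive control. For the EG–PCG comparison, treatment is therefore a within-person factor. The model named for the main aim has no term for treatment within person, for period or for sequence, and the text does not say whether it is fitted to phase 1 or to both phases.

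This is a mismatch between two things the article states, not a detail left to an analysis plan. At stake are the precision of the main comparison, the validity of its standard error if both phases are stacked, and whether the comparison with conventional physiotherapy can be made at all. The same data could be analysed in three materially different ways under the present wording.

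**Working it through.** **The plan's own figure.** The stated sample size is 93 before dropout (f = 0.15, alpha 5%, power 95%, three groups). Neither the number of measurements m nor the correlation ρ between them is stated. For a repeated-measures group × time test, λ = f²·N·m/(1 − ρ), with df (k − 1)(m − 1) and (N − k)(m − 1).

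- k = 3, m = 6, ρ = 0.5 (assumed): λ = 0.0225 × 93 × 6 / 0.5 = 25.11, df 10 and 450, power 95%. This reproduces 93.
- k = 3, m = 3, ρ = 0.5: λ = 0.0225 × 93 × 3 / 0.5 = 12.56, df 4 and 180, power 81%; 95% power needs 141. Three measurements also lead to 93 at 80% power, or at 95% power if ρ is about 0.68.

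So 93 hints at six measurements but does not settle which reading was meant.

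**Inputs for the EG–PCG contrast.** Crossover participants: 2/3 × 93 = 62, so n = 31 per sequence; the ACG has 31. The unit is the SD of change within a phase. The correlation r between a person's two phase changes is not given, so a range is assumed.

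**Reading 1: phase 1 only.** SE = √(2/31) = 0.254. The test is valid, but phase 2 is unused. A within-person crossover estimate has SE = √((1 − r)/31), which is 0.127 at r = 0.5. The ratio is 2, a four-fold loss of information.

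**Reading 2: both phases stacked by condition.** The model takes SE = √(2/62) = 0.180 whatever r is, because it treats the same 62 people as two independent groups. The SE ratio is 1/√(1 − r). True type I error is 2·P(Z > 1.96 × ratio). Power is shown for an assumed true difference of 0.3 SD of change. Normal approximation throughout:

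| r | stacked SE | correct SE | ratio | type I error | power, stacked | power, paired |
|---|---|---|---|---|---|---|
| −0.2 | 0.180 | 0.197 | 0.91 | 7.4% | 39.6% | 33.2% |
| 0 | 0.180 | 0.180 | 1.00 | 5.0% | 38.6% | 38.6% |
| 0.3 | 0.180 | 0.150 | 1.20 | 1.9% | 36.5% | 51.5% |
| 0.5 | 0.180 | 0.127 | 1.41 | 0.6% | 34.1% | 65.6% |
| 0.7 | 0.180 | 0.098 | 1.83 | <0.1% | 29.8% | 86.2% |

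Stacked power is P(estimate > 1.96 × 0.180), with the estimate varying by the correct SE. Simulation (4,000 runs) agrees on type I error: 5.3% at r = 0, 2.8% at r = 0.23 and 0.7% at r = 0.5.

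Period effects under stacking: let every phase 2 change shift by π. With equal sequences, the balanceHOME mean and the passive mean each rise by π/2, so the EG–PCG difference moves by π/2 − π/2 = 0. The ACG has phase 1 only, so a stacked comparison with it moves by π/2 − 0 = π/2.

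**Reading 3: group as randomised sequence, six times.** Let D be a person's phase 1 change minus phase 2 change. The treatment estimate is half the difference in mean D between sequences, with variance ¼ × 2 × 2(1 − r)/31 = (1 − r)/31. Pairing is kept. But for EG and PCG this single contrast is one of (2 − 1)(6 − 1) = 5 degrees of freedom in the group × time test, and the article does not name it. The ACG has three assessments and drops out of a complete-case MANOVA on six times.

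**The case against.** The strongest defence is the third reading. Section 2.3 assigns people to one of two groups for the crossover, section 2.4 calls EG and PCG the randomised groups and analyses by assignment, and 93 is reproduced with six measurements. Nobody is then entered twice. This stands as far as it goes, so a reader who infers that the model cannot analyse the crossover at all, or that its standard errors must be wrong, goes beyond the documents. What remains is that the treatment and period contrasts are unstated and the ACG cannot be included.

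A reader might also infer that stacking biases EG–PCG through progression or repeat testing. Under 1:1 allocation, a shift common to both sequences cancels. In simulation with a 0.5 SD shift and no treatment effect, the mean estimate was 0.003 and 4.0% of tests rejected. Period effects add noise there, not bias, apart from unequal dropout. They do not cancel against the ACG.

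Nor do the documents support a claim of excess false positives. With positive r, the stacked test is conservative. The relevant r concerns changes, which already remove a person's stable level. Under compound symmetry it is ρ − ρ − ρ + ρ = 0, and stacking then costs nothing in standard error. Only negative r makes the stacked error too small.

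**Conclusion.** The concern holds in this form: the model stated for the main aim does not match the crossover stated in section 2.1, and none of its three readings delivers both within-person control and a comparison with all groups. Phase 1 alone is valid but gives up the crossover (SE 0.254 against 0.127 at r = 0.5). Stacking leaves the EG–PCG standard error 1.00 to 1.83 times the correct one for r from 0 to 0.7, and lets period effects into the comparison with the ACG. The sequence reading keeps pairing but leaves the treatment contrast unstated and the ACG out.

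The sizes rest on complete data for 31 per sequence, unadjusted change, and assumed values of r and of the 0.3 SD difference. The documents support no particular r. The mismatch itself needs none of these assumptions. It should be settled before the data are analysed.

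**What to change.** Split the main analysis in two.

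1. **balanceHOME versus passive control, EG and PCG only.** Fit a linear mixed model (SPSS MIXED) to CoP sway area at T1 and T2 of both phases. Fixed effects: treatment, phase, sequence, visit, treatment × visit, that phase's T0 and the person's mean T0. Random effects: participant and participant-by-phase, or an unstructured within-person covariance. A participant effect alone is not enough with two visits per phase: simulated type I error (62 people, baseline omitted) was 8.7%, 11.0% and 14.8% when the person-by-phase variance was 0.25, 0.5 and 1 times the residual.
2. **balanceHOME versus conventional physiotherapy.** Compare EG with ACG in phase 1 only, adjusted for T0, labelled non-randomised, with no sequence term. Putting all three groups into one model with sequence does not work. The ACG sequence column equals the conventional-treatment column, so the six columns (intercept, two treatment, phase, two sequence) have rank 5.

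Where a result uses phase 1 only, say so and do not claim within-person control for it. The cost is revised analysis wording and a little more analysis work, with the same data and software.
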